### Recruitment and enrolment

During weekdays, patients transferred to G-OUH ward are screened for eligibility by a project coordinator in accordance with the criteria described above. Eligible patients are invited as soon as possible. Patients transferred to G-OUH during weekends are screened for eligibility on the first weekday. Patients that are hospitalised late Friday or Saturday and discharged during the weekend are likely missed (Table 1, Fig. 1).

**Table 1 Tab1:** SPIRIT—Schedule of enrolment, allocation, assessments, intervention, and follow-up

**Time point**	**Enrolment** **-** ***t*** _**1**_		**Allocation**	**Intervention**	**Follow-up**			
		Admission	Discharge	Home-visit 2–5 days	30 days	90 days	180 days	1 year
Enrolment								
Eligibility screening	X							
Informed consent	X							
Demographic data		X						
Data collection								
Barthel-100 ADL Index		X						
Clinical Frailty Scale			X					
Multimorbidity			X					
Polypharmacy			X					
Charlson Comorbidity Index			X					
Vital parameters			X	X				
Length of Stay			X					
Discharge diagnoses			X					
FS3 Nursing Problem Areas			X	X				
Discharge Questionnaire			X					
Post-Discharge Questionnaire					X			
Allocation			X					
Intervention Planning			X					
Intervention				X				
POCT Measurements				X				
Follow-up data								
Mortality data					X	X	X	X
Readmission data					X	X	X	X

**Fig. 1 Fig1:**
[figure not shown]
Study design

Eligible patients are informed about the project (orally and in writing) and invited to join. If they accept, they sign an informed consent. They are randomised on the day of discharge to either the intervention or control group. In the case of a planned discharge during the weekend, the participants are randomised on Friday. Participants randomised to the control group receive a usual discharge, while participants in the intervention group receive a usual discharge as well as a coordinated follow-up visit, which is planned to take place 2–5 working days after the day of discharge.

For all participants (control and intervention), administrative and clinical data will be collected from hospital records and the hospital administrative system, e.g. hospital discharge diagnoses, LOS, medication, medical history, Charlson Comorbidity Index [29] and Barthel Activities of Daily Living (ADL) score.

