### Blinding

The participant, hospital staff and project coordinator are blinded to the allocation until the participant is discharged upon which the randomisation occurs. Thus, the hospital treatment and discharge should not be affected by the enrolment of the participant. After discharge, when the patient is randomised, the participant, the project coordinator, the geriatric nurse, the community nurse, and the primary care physician will no longer be blinded. The project coordinator is not involved with the patients after the patient has been discharged, except if the patient is readmitted and invited to participate in the project again.

Prior to data analysis, all IDs will be linked to a new scrambled ID, and the old ID is hidden as will all identifying data (social security number, address). This will be done by a third party to ensure that the data analyst will not know which group is the intervention and which is the control group. All data analysis will thus be done blinded.

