### Data collection

Data will be collected at several points. The data will all be saved and stored in a secure database (REDCap). All personnel involved will be trained data collection.

Before the participant is invited to join the study, data is gathered on eligibility (i.e. diagnosed moderate to severe dementia, residence location to identify citizens of Odense Municipality, and type, use of home care, terminal diseases and presence of delirium).

Before discharge, data is gathered from the participants’ electronic medical records regarding discharge diagnoses, LOS, medication, medical history and Barthel ADL score [39]. A Clinical Frailty Score [40] is assessed by a geriatric nurse.

All data collected during the follow-up visit is registered in our database, including the data gathered in the FS-III survey, vital status and POCT results. The vital parameters and POCT results will be used to understand their influence on the clinical decision making.

The data collected during the follow-up visit will be filled directly into pre-defined fields in REDCap and will help ensure that all the necessary data is collected.

All participants, controls and interventions will receive a questionnaire, which is a modified version of a previously validated questionnaire [41]. At the time of randomisation, both groups will be asked about their satisfaction with the treatment, care and hospitalisation in general, as well as if they feel safe being discharged. A follow-up questionnaire will be administered to both groups by telephone. Data will be transferred to REDCap manually. The questionnaires will be administered by project coordinators who are not involved in the clinical care of the patients.

Data on death and readmissions will be collected from electronic medical records for 1 year after the allocation date for each participant.

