Previous studies using follow-up visits have shown positive effects when carried out by a geriatric team consisting of a physician and a nurse or allied health professional [14, 15]. However, as personnel resources are scarce, we aim at a cross-sectoral intervention with a trained geriatric nurse, a systematic assessment of functions (FSIII), POCT equipment for rapid clinical assessment, real-time video consultation with a geriatrician from the discharging hospital ward, and, not the least, a cross-sectoral face-to-face communication with the municipal care providers, the participants and possible relatives. This is a novel approach that, to our knowledge, has not previously been investigated. The intervention is multifactorial. As such, we will not be able to disentangle whether it is the coordinated home visit alone, the systematic approach, the clinical in-home assessment or the video consultation that is the most important. The present study is a pragmatic trial, based on the principles of Clinical Geriatric Assessment (CGA), with a holistic and cross-sectoral approach.

This study has several strengths and weaknesses. In terms of strengths, the study is a major RCT and thus it will yield a high level of evidence. The coordinator, who randomises the participants, will have no influence on treatment and care of the participants and thus no effect on readmission. The randomisation will be carried out at discharge, not during the admission, which ensures that the hospital staff is blinded and thus unbiased. As it is an RCT study, the survivorship bias will be low.

An additional strength of this study is that we also analyse the health economic aspects of the intervention, which is expected to be an important factor for potential adoption of this intervention in other clinical settings treating care needing older adults, e.g., orthopaedic departments discharging hip fracture patients. Equally important is the qualitative data from the user’s perspective.

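### Planned weekend discharges are allocated on Friday, during the admission, so the stated blinding until discharge is untrue for them; and for all participants the discharge questionnaire is not placed before disclosure

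*Protocol article*

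**What the plan says.** **Time of randomisation.** Under Recruitment and enrolment, in the text below Fig. 1, the general rule is: "They are randomised on the day of discharge to either the intervention or control group". The next sentence makes an exception: "In the case of a planned discharge during the weekend, the participants are randomised on Friday".

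**Blinding.** The Blinding section says: "The participant, hospital staff and project coordinator are blinded to the allocation until the participant is discharged upon which the randomisation occurs". From this it concludes: "Thus, the hospital treatment and discharge should not be affected by the enrolment of the participant". It then has the participant, the coordinator, both nurses and the primary care physician unblinded once randomisation has taken place, which it puts after discharge. The Discussion counts this as a strength: "The randomisation will be carried out at discharge, not during the admission, which ensures that the hospital staff is blinded and thus unbiased". Neither section mentions the Friday exception.

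**Discharge questionnaire.** The Data collection section says: "At the time of randomisation, both groups will be asked about their satisfaction with the treatment, care and hospitalisation in general". The same sentence adds whether they feel safe about going home. On who asks: "The questionnaires will be administered by project coordinators who are not involved in the clinical care of the patients". Table 1 puts the questionnaire and the allocation in the same discharge column and gives no order.

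**Who learns the group, and when.** Under Randomisation procedure the list is hidden from project users, REDCap gives the group to the coordinator in connection with discharge, and the coordinator takes no part in treatment or care. Under Intervention the municipality is called only once the participant is both assigned and discharged.

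**Time origins.** Table 2 counts 30- and 90-day readmission, and days alive out of hospital, from discharge. The Data collection section gathers deaths and readmissions for one year from the allocation date.

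**The concern.** The Background faults a recent Danish trial in the same kind of patient because its ward staff knew the allocation. Randomising at discharge is this trial's answer to that weakness: if nobody knows the group while the patient is in hospital, inpatient care and preparation for discharge cannot differ by arm. For planned weekend discharges that protection is not in place as described. If the group became known on Friday, staff or participant could act on it before the point from which readmission is counted, for instance in how the discharge is prepared.

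The questionnaire raises a related matter that is not confined to weekends. A participant who already knows that two nurses will visit may report feeling safer about going home than one who knows that no visit will come. An answer given after disclosure would then no longer be a pre-intervention measure that is comparable between the arms.

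**Working it through.** The point turns on wording, so the statements are set side by side.

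1. **Planned Saturday or Sunday discharge.** Allocation is on Friday. Saturday minus Friday is 1 day and Sunday minus Friday is 2 days, so allocation precedes discharge by one to two days and falls within the admission.
2. **Against the Blinding section.** That section makes randomisation and discharge coincide. In step 1 they do not. Since it also ties unblinding to randomisation, a literal reading would unblind participant and geriatric nurse on Friday. The other reading, that the result is held back until discharge, is not stated anywhere.
3. **Against the Discussion.** It denies that randomisation happens during the admission. For step 1 it does.
4. **Who can know early.** The coordinator runs the randomisation and receives the group from REDCap. Early knowledge by the coordinator is therefore the minimum that follows from a Friday randomisation, unless the display is delayed. For participant and ward the article records neither disclosure nor a barrier to it.
5. **Questionnaire.** It is tied to randomisation for both arms, and the people who administer it are coordinators, the role that receives the allocation. The order of asking and revealing is not fixed.
6. **Time origin.** The 30- and 90-day outcomes run from discharge, so Friday allocation does not move them. Only the one-year collection window starts at allocation. For this subgroup it starts 1 to 2 days early, which is 1/365 = 0.3% to 2/365 = 0.5% of the window.

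**How many participants.** The article gives no share of weekend discharges. Its planned enrolment is 763 × 1.2 = 915.6, rounded up to 916 per group, and 2 × 916 = 1832, which matches the stated total. Applying assumed shares:

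| Assumed weekend share | Share × 1832 | Participants |
|---|---|---|
| 5% | 91.6 | 92 |
| 10% | 183.2 | 183 |
| 20% | 366.4 | 366 |
| 2/7 (discharges even over the week) | 523.4 | 523 |

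These are counts of people allocated before discharge. They do not measure bias, and nothing in the article allows a size or direction of bias in the relative risk to be estimated. No input to the sample size changes.

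**The case against.** The strongest reply is that allocation is not disclosure. A reader might infer that ward staff and participants are told on Friday, and that the weekend discharge or its preparation then differs by arm. The documents do not support this. The coordinator gives no care, the list is hidden, the municipality hears only after discharge, and no section says that the ward or the participant is informed on Friday. There is also limited room to act: the discharge is already planned, agreed with the municipality and notified 24 or 48 hours ahead. This stands, and it makes influence on care an open risk only. It does not rescue the Blinding section, which names the coordinator among those blinded until discharge, nor the Discussion, which is wrong about when randomisation happens whoever knows the result.

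A second tempting reading is that the questionnaire is contaminated. The article does not say that it follows disclosure. An article may leave the order within a day to the full protocol, and the questionnaire serves the secondary outcome on user perspectives, not readmission. What remains is that the text fixes the questionnaire at the one moment where the order matters, and leaves that order open.

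A third is that Friday allocation shifts time zero for the primary outcome. It does not, because that outcome is counted from discharge.

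Finally, Friday allocation is openly stated and fits a coordinator who screens on weekdays. That explains the practice but does not reconcile it with the other two sections.

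**Conclusion.** The contradiction is explicit and holds for planned weekend discharges. They are randomised one to two days before leaving hospital, so two statements are untrue for them: that participant, staff and coordinator are blinded until discharge, and that randomisation does not happen during the admission. At least the coordinator can know the group, and no stated safeguard keeps it from the participant or the ward. Separately, for all participants, the discharge questionnaire is not placed before disclosure.

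The conclusion goes no further than that. Influence on care or on answers is possible but not documented. The number affected is unknown; 92 to 366 rests on an assumed share of 5% to 20%. The time origin of the primary outcome and the sample size are untouched. The point deserves correction because the property at issue is one that the article presents as a main strength, and because the remedy is cheap.

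**What to change.** **For any participants still to be enrolled.**
- Keep Friday randomisation if it is needed, but neither display nor disclose the result to coordinator, ward or participant until the participant has left hospital. The result could be released on the first working day afterwards.
- Complete the discharge questionnaire before disclosure for everyone.

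Scheduling should be little affected. After a Saturday or Sunday discharge, Monday is the first working day and the visit window on working days 2 to 5 runs from Tuesday to Friday, so release on Monday comes before it opens. The Aim gives the window in days without the word working. Counted in calendar days it is Monday to Thursday after a Saturday discharge and Tuesday to Friday after a Sunday one, so release on Monday still leaves at least three weekdays after that day. The cost is a change in the coordinator's routine and a delayed display.

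Moving randomisation itself to Monday would also remove the contradiction, but it is a trade-off. Patients who die or are readmitted over the weekend would drop out before allocation. That does not bias the comparison, but it removes events from the first week, which the article calls the period of highest risk. Withholding the Friday result keeps these patients in the intention-to-treat set.

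**For participants already enrolled.** The trial began in November 2022 with about 24 months planned, so recruitment may be over.
- Correct the Blinding section and the Discussion so that they state the Friday exception.
- Report how many participants in each arm were allocated before discharge, and who knew the group before the participant left.
- State whether the questionnaire was completed before disclosure.
- Add a sensitivity analysis of 30-day readmission that excludes Friday allocations made for a planned weekend discharge. Define the exclusion by the plan recorded before allocation, not by the actual day of discharge, which knowledge of the group could have altered. At an assumed 20% share it would keep 1832 − 366 = 1466 participants.
- Count the one-year follow-up from discharge, as for the 30- and 90-day outcomes.

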### Intervention and usual care

#### All participants

All participants giving informed consent receive the usual care, i.e., diagnostics, medical treatment and care by geriatricians, geriatric nurses and therapists. The usual discharge procedure is as follows: When a patient is close to not needing daily medical assessment by a ward geriatrician, a discharge date is set. A geriatric nurse communicates digitally with the municipal home care about the patient’s care needs in the home setting, including information about the patient’s in-hospital needs of personal care, need for aids and appliances and help with medication. The information also includes an overview of the in-hospital treatment. The patient is not discharged until the municipal home care is ready to provide the patient with the required help for personal care as jointly decided by the hospital staff and the municipal home care. In the case of increased home care requirements compared to before admission, the municipal home care is given a 48-h notice before discharge. If there is no increase in the level of home care, the notice is given 24 h before discharge. Due to these notices and that the average admission is longer than 48 h, the discharge is planned ahead of time and so-called “bed blockers” are very rarely a problem. If the patient is not discharged within the given time frame the municipality must pay a daily tariff to the hospital. The primary care physician receives an electronic discharge letter written by the discharging geriatrician, detailing the in-hospital treatment, test results, health status at discharge, changes in medication, diagnoses and need for follow-up in primary care or in hospital outpatient clinics.

#### Usual care

Participants are discharged according to the procedure described above.

#### Intervention

Participants receive the same discharge procedure as the control group. In addition, an appointment is made with the participant for a follow-up visit by a geriatric nurse and a community nurse in the participant’s home. The project coordinator in charge of recruitment and randomisation calls a municipal home care coordinator when the participant has been assigned to the intervention group and discharged. The municipal home care coordinator informs the community nurse assigned to the participant, who then calls a geriatric nurse coordinator to set a date and time for the coordinated follow-up visit on a weekday within 2–5 working days after discharge. We do not expect adherence issues due to the intervention being a one-time event very close to acceptance of inclusion. Thus, we employ no strategies to improve adherence. We do not restrict any concomitant care in relation to the intervention.

At the follow-up visit, the participant, a geriatric nurse and a community nurse from the care district, to which the participant belongs, are all present. Relatives are welcome to participate and the participant is encouraged to invite them.

The geriatric nurse brings along:

- A laptop with access to the OUH electronic patient record system and a secure video channel. Medical equipment for assessing vital status (pulse oximeter, electronic sphygmomanometer, thermometer) and body weight.- POCT technology for bed-side testingUltrasound bladder scanner (ultrasound device “Butterfly IQ + ”) [30].Analyses of blood samples with immediate resulti.HemoCue WBC DIFF Microcuvettes: Leukocytes, Neutrophiles, Lymphocytes, Monocytes, Basophiles, Eosinophiles. Capillary or venous [31].ii.I-STAT CHEM8 + Cartridge: Sodium (Na^+^), Potassium (K^+^), BUN/Urea, Creatinine, Haematocrit, Haemoglobin, Venous. Validated [32, 33].iii.QuikRead Go CRP + Hb Cartridge: CRP, Hb. Capillary [34].

At the visit, the participant, the geriatric nurse and the community nurse conducts a systematic assessment of the participant’s health and register any health-related problems. The assessment is conducted using a standardised Danish tool designed specifically for this purpose (Fælles Sprog III (FS-III) *(In English: Common Language III)*). Only a subsection of the tool, i.e. the parts covering mental well-being and bodily functions is used (“Helbredstilstande” (*In English: Health conditions*)). The tool is well known and used in the Danish home care system [35]. The Fælles Sprog III data is collected for the sole purpose of ensuring a systematic assessment.

For each item in the FS-III the geriatric nurse notes any changes in the participants’ health status, and whether the care plan has been followed, or deviations have been made. Adjustments to the care plan are made and noted accordingly. If there is any cause for concerns regarding the participant’s health compared to the time of discharge the geriatric nurse carries out vital status assessments. Further assessment by ultrasound bladder scan and/or bedside analyses of blood samples for C-reactive protein and electrolytes is based on the geriatric nurse’s clinical judgement. If the geriatric nurse finds it relevant, a geriatrician from G-OUH may be contacted by video. The geriatrician is thus able to communicate with the participant and the geriatric nurse, get the on-site clinically objective results, and finally make a clinical decision. If needed, the participant can be assessed the following day in the geriatric outpatient clinic or be acutely readmitted to the AMU.

### Randomisation procedure

The randomisation is a permuted block randomisation with block sizes 4, 6 and 8. This lowers the risk of having more follow-ups in a single week than we can manage. The permuted blocks are made to ensure that the coordinator and the staff will not be able to predict the result of the randomisation. The coordinator is not involved in the participant’s treatment or care at all, neither before nor after randomisation. We are using equivalent group distribution to maximise statistical power. There are more blocks than needed, which ensures that the final block sizes cannot be predicted.

In practice, the randomisation procedure is handled by Open Patient data Explorative Network (OPEN) [36], a research support entity also in charge of the REDCap database, a database made specifically for enrolling, randomising, data collection and data management. The allocation sequence is made by OPEN and based on a pseudo random number generator (RNG) list. It is made using software by Sealed Envelope Ltd [37], a widely used service. The list is not from a true RNG, as it has a seed^1^ to recreate the list [37]. This seed and the list, however, is unavailable to the coordinator that assigns a group to the participants (and unavailable to everyone else in the core group of this project as well—the seed is in the possession of OPEN and the list is hidden from the users involved in the project in the REDCap software). REDCap will tell the coordinator which group the participant will be in upon discharge.

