### Study design

The study is a single-centre two-arm parallel group randomised controlled trial with an aim to show superiority. It will utilise permuted block randomisation without stratification. Distribution will be equivalent between the two groups. The study will be conducted over approximately 24 months.

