### Eligibility

A project coordinator identifies eligible patients among all patients admitted to G-OUH.

Only patients transferred to G-OUH ward are screened for eligibility, and thus patients discharged directly from the AMU are not included.

Criteria for eligibility are patients admitted to G-OUH and discharged to their own home and in need of personal care provided by the municipal home care organisation in Odense Municipality. Patients discharged to care home are also included. Exclusion criteria are patients discharged to other skilled nursing facilities or discharged with no need for personal care. Also, terminally ill patients and incapacitated patients, e.g., patients with moderate or severe dementia are not eligible. Patients with dementia are excluded if they are unable to live independently (i.e., if they require a care home or are completely dependent on their spouses to remain at home). In cases of uncertainty, a senior geriatric consultant will assess the cognitive function and determine severity. Patients that are delirious throughout the entire hospital stay will also be excluded, as they cannot give informed consent. Patients with active delirium are reassessed by a project manager based on indications such as confusion to orientation (to personal data, treatment, location, time and recent events), ability to concentrate and follow a conversation, organisation and coherence of thought, and overall mental status, as assessed by the CAM score. In cases of uncertainty, patients are not included. Finally, while initially excluding readmitted patients who had already been enrolled as study participants, it was decided after 4.5 months from the start of the study to allow the inclusion of readmitted study participants. The change was made due to an insufficient entry of eligible participants following a shortage of staff and a cut in the number of hospital beds at G-OUH. The original eligibility criteria were thus slightly changed to allow readmitted patients to participate. We decided to include these patients due to the uncertainty of future patient flow, knowing that we can adjust for this factor in the analyses after the trial.

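### Permuted blocks of 4, 6 and 8 do not stop the coordinator predicting the next allocation: on this single list about 68% can be guessed, which matters when several consented patients are randomised on the same day

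*Protocol article*

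**What the plan says.** Under Study design the article describes one centre, two arms in equal numbers, and no strata: "It will utilise permuted block randomisation without stratification". Under Randomisation procedure it gives the block sizes, "The randomisation is a permuted block randomisation with block sizes 4, 6 and 8", and two reasons for blocking. One is to limit the number of follow-up visits falling in a single week. The other is concealment: "The permuted blocks are made to ensure that the coordinator and the staff will not be able to predict the result of the randomisation".

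The same section says that the list and its seed are held by the research support unit and hidden from the project group, that more blocks exist than are needed, and that the coordinator takes no part in care. It also says: "REDCap will tell the coordinator which group the participant will be in upon discharge". The Intervention section shows that one role both recruits and randomises: "The project coordinator in charge of recruitment and randomisation calls a municipal home care coordinator". The Blinding section confirms that the coordinator is no longer blinded once a participant has been randomised.

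On timing, Recruitment and enrolment places consent during the stay and randomisation on the day of discharge. Planned weekend discharges are randomised on the Friday before.

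**The concern.** Blocking forces the arms back to equality at the end of every block. Anyone who has seen the earlier allocations therefore knows something about the next one. Hiding the list and seed does not hide past allocations, and spare blocks at the end protect only the last block.

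The Discussion offers this reassurance: "The coordinator, who randomises the participants, will have no influence on treatment and care of the participants and thus no effect on readmission". That deals with bias from differential care. It does not deal with selection, meaning which patient is given the next place on the list. If a frailer or healthier patient could be matched to a predicted arm, the arms would differ in baseline readmission risk, and the difference would look like an effect of the visit. The article counts randomisation at discharge among its main strengths, so the description of concealment should be accurate.

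**Working it through.** The article gives no figure for predictability, so there is none to reproduce. The check asks how often the next allocation can be guessed by someone who knows all earlier ones.

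**Inputs from the article**
- Block sizes 4, 6 and 8 (Randomisation procedure).
- One centre, one list, no strata, equal allocation (Study design).
- The coordinator is told each allocation (Randomisation procedure; Blinding).

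**Assumption.** The mix of block sizes is not stated. Equal frequency is assumed, and other mixes are shown.

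**Rule for guessing.** Name the arm that is behind in the running count, and toss a coin when the count is level. Every block ends level, so the running count on a single list is also the count within the current block. The guesser does not need to know where blocks begin or how long they are.

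**Formula.** In a block of 2m allocations, the expected number of correct guesses is m + 2^(2m−1)/C(2m, m) − 1/2.

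| Block | Calculation | Expected correct | Share |
|---|---|---|---|
| 4 (m = 2) | 2 + 8/6 − 0.5 | 2.833 | 70.8% |
| 6 (m = 3) | 3 + 32/20 − 0.5 | 4.100 | 68.3% |
| 8 (m = 4) | 4 + 128/70 − 0.5 | 5.329 | 66.6% |

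Equal mix: (2.833 + 4.100 + 5.329)/(4 + 6 + 8) = 12.262/18 = 68.1%. The unequal mixes tried gave 67.7% to 68.6%.

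**Checks.** Full enumeration of each block size gives the same values. In a simulation of 40 lists of 1526, this rule was right 68.2% of the time, and a guesser using the best available probabilities without knowing block boundaries was right 68.0% of the time. The arms were level at 36.4% of allocations. At the other 63.6% the guess was right 78.6% of the time: 0.364 × 0.5 + 0.636 × 0.786 = 0.68.

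**What the varied sizes achieve.** If block boundaries were known, the share of allocations known with certainty would be 33% for blocks of 4, 25% for 6 and 20% for 8. With sizes mixed and boundaries unknown it is about 2%. Mixing removes most certain knowledge but leaves the average hit rate at about 68%.

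**Effect of consenting earlier.** If k consented patients are still to be randomised before the patient now being approached, the best guess for that patient falls:

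| k | Best guess correct |
|---|---|
| 0 | 68% |
| 1 | 60% |
| 2 | 57% |
| 3 | 53% |
| 5 | 51% |

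The 68% therefore applies at the moment of randomisation, not at recruitment.

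**The case against.** The strongest reply is that the design already separates selection from allocation. Patients are invited soon after transfer and randomised only at discharge. The discharge date is set clinically, with notice to the municipality, so the coordinator does not control it. This stands. With several consented patients waiting, prediction at consent is close to chance, and what remains is the order of entry among patients already due for randomisation on the same day.

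It is also fair that 68% includes the 50% obtained by tossing a coin, so the gain is about 18 points, and that a hit rate is not an estimate of bias. Varied blocks on an externally held list are conventional. A journal article may leave entry order to the full protocol, so its silence on order is not itself the fault. The fault is the stated assurance.

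Three stronger readings are tempting but unsupported:

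- A reader might infer that the coordinator could drop a patient just before randomisation under the rule "In cases of uncertainty, patients are not included". Under Eligibility, that rule closes the account of delirium reassessment by a project manager. It concerns ability to consent and so acts before consent. Uncertain dementia goes to a senior consultant.
- A reader might divide the target of 1832 by 24 months (1832/104 weeks = 17.6 a week, or 3.5 per weekday) and conclude that there is usually a choice of order. The sample size section expects only about 1500–1800 discharges from the whole department in 2022–2023, and Trial status reports fewer patients than planned. The rate is too high to rely on.
- A reader might conclude that the list should be replaced by simple randomisation. That is a trade-off against the workload control the blocks provide, made in mid-trial, and the finding does not require it.

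**Conclusion.** The point holds in a limited form. The blocks do not ensure unpredictability. On this list the next allocation can be guessed about 68% of the time (66.6% to 70.8% by block size; 67.7% to 68.6% over the mixes tried), with about 2% certain.

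The practical exposure is narrow: the order of entry for same-day discharges and for the Friday batch of weekend discharges. How often such a choice arises is unknown, no effect on the readmission comparison has been calculated, and nothing in the article suggests misuse.

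The figure assumes that whoever randomises knows all earlier allocations. The article speaks of the randomising coordinator in the singular, but of several coordinators for the questionnaires. If several people shared randomisation without sharing results, the hit rate would be lower. The assumed mix of block sizes barely matters.

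**What to change.** 1. In REDCap, require consent and the eligibility confirmation to be recorded and locked before the randomise function opens.
2. Enter patients due for randomisation on the same day, including the Friday batch, in a fixed order such as study ID, without skipping.
3. Report the number of patients who consented but were not randomised, with reasons. If recruitment has closed, report how same-day order was set.
4. Correct the sentence. Blocks control the weekly number of visits. Concealment rests on the hidden list and varied block sizes, which reduce predictability but do not remove it. Revise the Discussion sentence on the coordinator so that it claims only that care is unaffected.

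The cost is a REDCap setting, one procedural sentence, one extra line of reporting and an edit to the text. The allocation list, sample size and analysis are unchanged.
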